## 2. Materials and Methods

### 2.1. Study Design and Participants

The Active Learning in PHYsical Literacy (ALPHYL) study is a RCT in primary schools in Valencia (Spain) and its metropolitan area, with the schools as the units of randomisation and the students as the units of analysis. The design, implementation and reporting of ALPHYL will be carried out according to the CONSORT statement [25] and considering the SPIRIT recommendations. The sample will consist of at least 264 primary school Grade 5 pupils (i.e., 10–11 years old).

The sample size was calculated from previous studies that focused on the effects of interventions on PA and motor competence [11,22], using G*Power 3.1 software (University of Düsseldorf, Düsseldorf, Germany). From these studies, for an effect size between 0.30 and 0.32 with an alpha level of 0.05 and statistical power of 90%, the sample size had to be between 105 and 220 participants. To avoid reducing statistical power due to experimental mortality, the sample was increased by 20%, with the participation of 264 children. To recruit the participants, children from six schools (three intervention and three control schools; four public and two private) in Valencia and its metropolitan area will take part, consisting of pupils willing to participate and whose families provide signed informed consent (inclusion criterion). Pupils who present evident physical and mental difficulties that prevent them from satisfactorily completing all the measurements proposed in the study will not be included in the analyses (exclusion criteria). Only typically developing children will be included in the analysis.

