### 2.3. Procedure

The CONSORT study flow diagram is shown in Figure 1. A list of primary schools in Valencia and its metropolitan area will be obtained from the government educational institutions. The schools will be randomly selected and ordered in a list using computer-generated random numbers by a researcher from the study team. The inclusion criteria for the schools’ participations will be: (a) must have at least two groups of primary school Grade 5 pupils, and the teachers involved in both must agree to participate; (b) each class group includes at least 75% of the participants; and (c) children must not have taken part in other PA promotion interventions during the intervention period in the previous two years. If a school decides not to participate, the same procedure will be performed with the next school selected from the list. The six selected schools will also be randomly allocated to the intervention (*n* = 3) or control groups (*n* = 3). Students will be unaware of whether they have been allocated to the intervention or control group.

In order to detect barriers to and facilitators of the intervention’s adoption, implementation and sustainability, an instrument based on the reach, effectiveness, adoption, implementation and maintenance (RE-AIM) tool will be used to analyse its reach, effectiveness, adoption, implementation and maintenance [26], as well as its impact [8,26]. This instrument will be implemented with the teachers involved in the intervention, who will provide information on their teaching methods and the pupils’ participation by completing a personal teaching diary [13,27].

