### 2.5. Measurements

Table 2 describes the different primary and secondary outcomes that will be assessed. These indicators are classified into individual factors according to the different physical literacy domains and the environment created. All the measurements will be carried out during school hours in two PE lessons and two regular classroom lessons in each group for pre-test, post-test and retention.

During PE lessons, three measures will be performed: (1) Actual motor competence by using the Canadian Agility Movement Skill Assessment (CAMSA), a circuit-based field-test test [35,36] which combines product- and process-oriented fundamental movement skills measures. This test is feasible in PE classes [36]. (2) The Progressive Aerobic Cardiovascular Endurance Run (PACER) will also be used to assess cardiorespiratory fitness [50], as well as, (3) children’s weight and height. Barefoot weight and height will be measured once with participants wearing light clothes. The body mass index (BMI) will be calculated as weight in kilograms divided by height in square metres (kg/m^2^) and determined according to the children’s sex and age [49].

The pupils will be given a questionnaire in a classroom setting with different measures, including perceived motor competence [39,40] and physical literacy [38], motivation [41,42], perceived social support [43,44], active commuting to school [48], PA participation [42,51], alienation with school [52], future PA intention [43], psychological needs satisfaction [41], perceived body image [53], physical self-concept [54], sedentary behaviour [56], school satisfaction [57], social identity [58], knowledge related to PA and healthy lifestyles [41,59] and the measurement of math fluency calculation [60]. Two cognitive function tests, Stroop and digit-span tests [47], will be carried out individually, while academic achievement will be obtained from the final grade scores [45,46].

After these measurement sessions, each participant will be given an ActiGraph wGT3X-BT accelerometer (ActiGraph Corp ^®^, Pensacola, FL, USA, EEUU) to wear on a hip belt for 8 days [15], a method that has shown validity and reliability in assessing PA patterns in children [37].

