### 2.6. Data Management and Statistical Methods

To avoid possible bias in the data analysis, an independent blinded researcher will carry out a pseudonymisation process to guarantee the anonymity of the data. Missing data will be imputed using multiple imputation. According to our Institutional Review Board (IRB), a data monitoring committee will not be necessary since this is a low-risk study. Adverse events and protocol deviation will be documented by teachers using their personal teaching diary. Moreover, the research team will perform weekly audits to ensure data quality and the correct development of the protocol.

Independent researchers will also code actual motor competence videotapes so that they are stratified and counterbalanced. The video coded data, information from the individual questionnaires, accelerometer data and a family proxy-report of the participants’ residential neighbourhood will be hosted on an open access digital platform (zenodo.org) to be available to the scientific community.

The teachers’ data obtained in the semi-structured interviews will be categorised and thematically analysed by the NVivo^®^ qualitative analysis program (QSR International: Technology & Software Solutions, Burlington, MA, USA).

Structural equation modelling will be conducted to analyse the association and mediating role of some of the measured variables according to the conceptual models of children’s motor development and physical literacy [21,66]. To study the effect of the intervention on primary and secondary variables, linear mixed models will be built with the time, condition and interaction of time and condition as fixed effects, adjusting for baseline values. When a significant interaction effect is found, post-hoc tests will be applied by the least significant difference method. The data will be analysed on different statistical software, mainly SPSS (SPSS Inc., Chicago, IL, USA) and Mplus [67].

An analysis of the intervention effects in a person-centred approach will allow us to determine the children’s profiles according to their primary physical literacy outcomes (i.e., actual and perceived motor competence, motivation, perceived social support and cognitive function), while the trends and association will be analysed with the remaining physical literacy primary and secondary outcomes, for which self-organised maps will be created on MATLAB (MathWorks Inc., Natick, MA, USA).

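### The exclusion for physical and mental difficulties acts on the analysis set, with no time point and no assessor blind to allocation, so it can remove pupils after schools are randomised

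*Protocol article*

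**What the plan says.** Protocol article, section 2.1, gives willingness and signed family consent as the inclusion criterion for pupils. An exclusion follows for pupils whose difficulties, physical and mental and described as evident, "prevent them from satisfactorily completing all the measurements proposed in the study will not be included in the analyses". The text labels this as exclusion criteria. A further sentence then adds: "Only typically developing children will be included in the analysis".

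Section 2.5 schedules the measurements in "two PE lessons and two regular classroom lessons in each group for pre-test, post-test and retention".

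Section 2.6 states without qualification: "Missing data will be imputed using multiple imputation". It also plans linear mixed models adjusted for baseline values.

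On design, section 2.1 describes a trial "with the schools as the units of randomisation and the students as the units of analysis", and section 2.3 allocates six schools, three to each arm. Blinding is stated for the pupils (section 2.3) and for the researcher who pseudonymises the data (section 2.6). It is not stated for whoever applies the exclusion.

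**The concern.** An eligibility rule is harmless to a randomised comparison when it rests on facts that allocation cannot have influenced. This rule is not tied to such facts. It takes effect at analysis, depends on satisfactory completion of the whole set of measurements, and uses three terms that call for judgement: evident, satisfactorily and typically developing.

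The judgement bears on the outcomes. Motor competence, physical activity and cognitive function are all primary, and pupils with physical or mental difficulties would be expected to score low on some of them. If more such pupils were removed in one arm, that arm's mean would rise for a reason unrelated to the programme.

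The opportunity to notice difficulties may also differ by arm. Section 2.4 places three research assistants with the teaching team throughout the intervention and describes nothing comparable in control schools. That this would lead to more exclusions in intervention schools is an inference; the article does not say so.

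**Working it through.** The point rests on reading the rules together. The article gives no figure to reproduce here.

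**Step 1. Who is covered.** Only pupils with evident physical and mental difficulties (section 2.1). Absence, dropout or not wearing the accelerometer does not trigger the rule.

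**Step 2. Where it acts.** On the analyses. Consent and willingness are the only stated conditions for entry, so a covered pupil can be enrolled and measured, then removed.

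**Step 3. When it can be met.** The measurements recur at three waves (section 2.5), and two of the three follow the intervention. Nothing confines the difficulty, or its recognition, to the first wave.

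**Step 4. Whether the pre-test precedes allocation.** Table 1 puts teacher training in May–July 2022, resource preparation in September–December 2022 and the pre-test in January 2023. The date of allocation is not given. If allocation came before this preparation, even a pre-test judgement could be made with the arm known.

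**Step 5. Overlap with imputation.** Take a pupil whose difficulty causes missing post-test or retention data. Section 2.1 can be read as removing the pupil; section 2.6 imputes missing data. No order of precedence is given.

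**Step 6. Illustrative size.** Assume that a fraction q of one arm is excluded in excess of the other, and that these pupils lie 1 SD below that arm's mean. The mean of those who remain rises by q/(1 − q) × 1 SD.

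| q | Calculation | Shift, unadjusted |
|---|---|---|
| 0.05 | 0.05/0.95 | 0.053 SD |
| 0.10 | 0.10/0.90 | 0.111 SD |

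With 264/2 = 132 pupils per arm, these fractions are about 7 and 13 pupils.

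A harsher assumption is that the very lowest scorers on a normal outcome are removed from one arm. The shift is then φ(z_q)/(1 − q), where z_q is the q-quantile of the standard normal distribution and φ its density: 0.05 SD for 2%, 0.11 SD for 5% and 0.19 SD for 10%.

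**Step 7. Effect of baseline adjustment.** If exclusion follows the post-test score, and baseline correlates ρ with it, the baseline mean of the depleted arm also rises, by ρ times the shift. Adjustment with slope ρ leaves about (1 − ρ²) of the shift. With ρ = 0.7 (assumption), 1 − 0.49 = 0.51, so 0.053 becomes about 0.027 and 0.111 about 0.057 SD. If exclusion depends on baseline status alone, the adjusted shift is about zero.

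**The case against.** The strongest answer is that this is an ordinary eligibility criterion. It stands in the participants section, directly after the inclusion criterion, and carries the label of exclusion criteria. Typically developing describes a lasting characteristic of a child, not performance on a later test. Because the intervention is delivered to whole classes, leaving such pupils out of the analyses may only mean that they join the lessons without being study subjects. The measurements may mean the test battery rather than every wave. Assessor and timing could also stand in a fuller document that is not shown.

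This reading is plausible, and it keeps the point modest. It does not remove it, because the sentence as printed acts on the analyses and nothing in it confines the judgement to baseline. The mechanism is also conjectural: section 2.4 gives the research assistants support and monitoring tasks, not eligibility decisions, and evident difficulties leave limited room for new cases to come to light.

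Three stronger readings may tempt a reader, and the article does not support them.

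- *Any pupil who misses a test is dropped from every outcome.* The opening condition on physical and mental difficulties rules this out.
- *The exclusion contradicts multiple imputation.* One rule can define who is analysed and the other handle gaps among them. They meet only in the case of Step 5.
- *The bias could reach a third of the planned effect.* 0.111/0.32 = 0.35 and 0.111/0.30 = 0.37, but only if the planned 0.30 to 0.32 is a standardised mean difference. The article's lower bound of 105 participants reproduces with a two-group F test at f = 0.32, which equals d = 2 × 0.32 = 0.64; on that scale the share is 0.111/0.64 = 0.17. Both shares also ignore baseline adjustment.

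**Conclusion.** The concern holds in a limited form. As written, section 2.1 permits pupils to be removed from the analysis after allocation, on a judgement linked to the outcomes, without a stated time point or an assessor stated to be unaware of the arm. It also leaves open whether exclusion or imputation governs a pupil whose difficulty leads to missing later data.

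The article does not show that arm-dependent exclusion will happen, and it gives no rate from which to estimate a bias. The illustrative 0.05 to 0.11 SD rests on an assumed one-arm excess of 5 to 10% and an assumed 1 SD deficit. It describes the unadjusted difference; the planned adjustment would reduce it, possibly to near zero. The change is worth making because it is nearly free and closes the question before analysis.

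**What to change.** Replace the two sentences in section 2.1 with a rule that:

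- settles this eligibility once for each pupil, no later than the January 2023 pre-test;
- rests on a pre-existing condition, for example one recorded by the school, that does not depend on later test performance;
- is applied identically in all six schools by existing study staff unaware of the school's allocation. This matters even at pre-test, because the date of allocation is not stated.

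Then state that every eligible consenting pupil is analysed in the arm to which the school was allocated, and that later incomplete measurements, whatever their cause, are handled by the multiple imputation of section 2.6. That supplies the missing order of precedence.

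The cost is a few sentences of text and slightly more imputed values. No measurement procedure changes.

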### 2.2. Patient and Public Involvement

Students were not involved in the design of this study. Students and teachers will be involved in the conduct, reporting and dissemination plans of this research. The teachers of the schools involved in this study did participate in the design of this study. Moreover, we will continue to involve these teachers as we complete the study, through regular meetings to obtain their feedback on the study.

### 2.3. Procedure

The CONSORT study flow diagram is shown in Figure 1. A list of primary schools in Valencia and its metropolitan area will be obtained from the government educational institutions. The schools will be randomly selected and ordered in a list using computer-generated random numbers by a researcher from the study team. The inclusion criteria for the schools’ participations will be: (a) must have at least two groups of primary school Grade 5 pupils, and the teachers involved in both must agree to participate; (b) each class group includes at least 75% of the participants; and (c) children must not have taken part in other PA promotion interventions during the intervention period in the previous two years. If a school decides not to participate, the same procedure will be performed with the next school selected from the list. The six selected schools will also be randomly allocated to the intervention (*n* = 3) or control groups (*n* = 3). Students will be unaware of whether they have been allocated to the intervention or control group.

In order to detect barriers to and facilitators of the intervention’s adoption, implementation and sustainability, an instrument based on the reach, effectiveness, adoption, implementation and maintenance (RE-AIM) tool will be used to analyse its reach, effectiveness, adoption, implementation and maintenance [26], as well as its impact [8,26]. This instrument will be implemented with the teachers involved in the intervention, who will provide information on their teaching methods and the pupils’ participation by completing a personal teaching diary [13,27].

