#### Covariates

In addition to children’s sex and age, parental educational qualifications will be assessed to estimate the families’ socioeconomic status (SES) using a parental questionnaire. This will be assessed by the mother and father’s reported qualifications, something that was completed by any elementary, middle, high school or university [61].

The measurements of the perception of the characteristics of the participants’ home neighbourhoods will be carried out on the Neighbourhood Environment Walkability Scale for Youth (NEWS-Y-IPEN) questionnaire [62], which will be filled out by the parents. The NEWS-Y-IPEN provides information on the neighbourhood characteristics regarding aspects such as traffic safety, infrastructures, diversity of destinations, etc. (Table 3). The families will indicate their postal address to enquire into the objective characteristics of the home neighbourhood. Geographic information systems (GIS) and systematic observation tools will be used to analyse the environments, including the connectivity of the streets or the presence of the green areas that young people have at their disposal to maintain active behaviour. The physical school characteristics will be assessed in relation to PA [63,64] using an audit process. The schools’ neighbourhood environment will also be evaluated by GIS procedures and the Microscale Audit of Pedestrian Streetscapes (MAPS) Global audit tool [65].

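### As described, six schools (four public, two private) are allocated 3:3 with no restriction by school type, so 40% of possible draws put both private schools in one arm

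*Protocol article*

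**What the plan says.** Section 2.1 of the protocol article sets up a cluster design, "with the schools as the units of randomisation and the students as the units of analysis", and fixes the composition: "three intervention and three control schools; four public and two private". Section 2.3 describes how schools are drawn from a randomly ordered list and then states: "The six selected schools will also be randomly allocated to the intervention" or control arm, three schools to each. The 3:3 split is the only restriction given. Stratification is mentioned once in the article, in section 2.6, and there it concerns the coding of motor-competence videos.

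For the analysis, section 2.6 says: "linear mixed models will be built with the time, condition and interaction of time and condition as fixed effects, adjusting for baseline values". School type is not among these terms. Nor are the pupil covariates, although the Covariates part of section 2.5 and Table 3 list sex, age and parental education, the last for this purpose: "parental educational qualifications will be assessed to estimate the families’ socioeconomic status (SES) using a parental questionnaire".

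**The concern.** School type is known before allocation and there are only six units to allocate. With so few, an unrestricted draw will often leave the arms unlike each other on a visible school characteristic. One draw serves every primary outcome, so an unlucky split affects all of them together. Academic achievement is the most exposed, because it is taken from final grades.

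If public and private schools differ in pupil intake, resources or grading (an assumption; the article does not say so), part of that difference enters the estimated intervention effect. The effect model as written contains none of the collected covariates that could absorb some of it.

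**Working it through.** The article states no probability of imbalance, so there is no figure of its own to reproduce.

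**Inputs from the article.** Six schools, four public and two private, three per arm (section 2.1); random allocation with no other stated restriction (section 2.3); effect model with time, condition, their interaction and baseline values (section 2.6); planning effect size 0.30 to 0.32, alpha 0.05, power 90%, N between 105 and 220 (section 2.1).

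**Assumptions.** Equal-sized schools; a public-private outcome gap G of 0.2, 0.3 or 0.5 SD; a baseline to follow-up correlation r of 0.5 or 0.7. The documents give none of these.

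**Step 1: chance of imbalance.**
- All 3:3 allocations: C(6,3) = 20.
- Both private schools in the intervention arm: C(2,2) × C(4,1) = 4. Both in the control arm: 4.
- Probability that both share an arm: 8/20 = 0.40.
- One in each arm: C(2,1) × C(4,2) = 12, and 12/20 = 0.60.

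**Step 2: shift before baseline adjustment.** In the unbalanced case one arm is 2/3 private and the other 0/3, so the shift is (2/3 − 0/3) × G.
- G = 0.2: 0.13 SD
- G = 0.3: 0.20 SD
- G = 0.5: 0.33 SD

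**Step 3: what baseline adjustment leaves.** If the gap is stable over time, a change-from-baseline contrast cancels it. With the baseline value as a covariate and equal SDs at both times, about (1 − r) of it remains.
- r = 0.5: 0.13 to 0.33 becomes 0.07 to 0.17 SD.
- r = 0.7: 0.13 to 0.33 becomes 0.04 to 0.10 SD.

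If instead private and public pupils differ in their change over the study by D, the shift is (2/3) × D and baseline adjustment does not remove it. The documents give no value for D.

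**Step 4: can the shift be set against the planned effect?** The lower N of 105 is reproduced by a two-group F test with f = 0.32, which for two equal groups is d = 2 × 0.32 = 0.64. It is also reproduced by a two-occasion time-by-group test with f = 0.16 (d = 0.32) and correlation 0.5. The upper N of 220 was not reproduced at 0.30 in the variants tried (for example, 119 for f = 0.30 and 468 for a two-sided t test with d = 0.30). The metric therefore cannot be recovered. Against d = 0.64 the unadjusted shift is 0.13/0.64 to 0.33/0.64, roughly 20% to 52%; against d = 0.32 it is roughly 42% to 104%.

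**Step 5: allocation within school type.** Choosing one of two private and two of four public schools for the intervention arm gives 2 × 6 = 12 allocations. Each arm is then 1/3 private, so the school-type imbalance is zero. The smallest two-sided permutation p on schools rises from 2/20 = 0.10 to 2/12 = 0.17.

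**The case against.** The strongest objection is that the absence of restriction is read from silence. Section 2.3 is also silent on how the mix of four public and two private schools was obtained, yet section 2.1 fixes that mix, so school type was handled somewhere that the section does not describe. The article is condensed and its flow chart is not available here; a fuller protocol could specify stratified allocation. This stands as a limit: the 40% belongs to the allocation as described.

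A reader might also infer that the possible shift is as large as the effect the trial is powered for. The documents do not support this. The gap is assumed, the shift in step 2 is for an unadjusted difference that the plan does not use, and the planned effect size has no stated metric.

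A reader might further infer that in an unlucky draw school type could not be separated from the intervention. That is too strong. Public schools remain in both arms, so the two are not collinear and a school-type term is estimable, though imprecise with six schools.

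It can also be said that this is chance imbalance under valid randomisation and that the choice of covariates is often left to an analysis plan. The first is correct. The second carries less weight here, because the article does list the fixed effects of its model and its own named covariates are not among them.

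**Conclusion.** The point holds as an inexpensive improvement to the design and model; it does not show that the trial is biased. For the allocation as described, the 40% chance that both private schools share an arm is exact. Its consequence is conditional: 0.13 to 0.33 SD before baseline adjustment for an assumed gap of 0.2 to 0.5 SD with equal-sized schools, and about 0.04 to 0.17 SD after covariate adjustment for a stable gap with r between 0.5 and 0.7. A school-type difference in change would pass through baseline adjustment, and its size is unknown. These figures illustrate the risk; none is an estimate from the documents.

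**What to change.** State the allocation method in section 2.3. If allocation is still open, randomise within school type, so that each arm receives one private and two public schools. In section 2.6, add pupil sex, age and parental education as fixed effects in the effect model. They are already collected, they are pupil-level and so use no school-level degrees of freedom, and the planned multiple imputation can cover unreturned parental questionnaires. Parental education will stand in for school type only in part, so it supplements balanced allocation and does not replace it.

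Table 1 dates the intervention January to March 2023, so allocation may already be done. In that case report the public/private split by arm, keep the covariate adjustment, and interpret the effect with that split in view.

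The cost is a changed random list and one line in the model, with no added schools or data. The downside is 12 instead of 20 possible allocations, which raises the smallest two-sided school-level permutation p from 0.10 to 0.17. Neither could reach 0.05, and the planned analysis is model-based, so little is lost. Balance is exact only if the schools are of similar size.
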